## 1. Abstract/Summary

Provision of vaccines through immunization campaigns is crucial to control outbreaks of vaccine-preventable diseases (VPDs) because they provide individual protection and herd immunity. Several vaccination campaigns, targeting primarily children under 15 years in the Forcibly Displaced Myanmar Nationals (FDMN) camps and settlements, have been conducted to reduce the risk of disease and prevent outbreaks. However, outbreaks of measles and diphtheria have been documented in these communities. To better understand the impact of vaccination activities conducted in closing immunity gaps and preventing new outbreaks, the United Nations Children's Fund (UNICEF), World Health Organization (WHO) and U.S. Centers for Disease Control and Prevention (CDC), in collaboration with the Bangladesh Government EPI Program and Institute of Epidemiology, Disease Control and Research (IEDCR), propose an assessment of vaccination coverage in a representative sample from the FDMN camps and settlements using a vaccination coverage assessment questionnaire and collection of dried blood spot (DBS) for serologic analysis of immunity.

The vaccination coverage assessment questionnaire is an excellent tool to assess vaccination coverage and identify barriers for accessing immunization, but using it to estimate gaps in population immunity will be challenging in the FDMN population because of the low retention of cards from vaccinations campaigns, difficulty recalling vaccine doses after multiple campaigns over numerous months, and the uncertainty of vaccination status in Myanmar. Thus, we propose to conduct a serological assessment by DBS simultaneously with the coverage assessment questionnaire in order to better estimate the proportion of individuals (especially among recent arrivals) that remain un- or under-protected against the diseases targeted by the vaccination efforts.

We propose to select a representative sample of households in Kutupalong Registered Camp, Nayapara Registered Camp, and the makeshift/informal settlements. In the formal camps, simple random sampling of households will take place; in the makeshift/informal settlements, we will use a multi-stage cluster approach. In each selected household, we will randomly select one child 6 months–6 years of age and one child aged 7 years–14 years. For each child, we will conduct a short interview in Rohingya in or near the home with the available caregiver using a standardized vaccine coverage assessment questionnaire to assess vaccines received during the campaigns and elsewhere, as well as barriers for receiving vaccination during the most recent vaccination campaign. Available vaccination cards will be reviewed to record documented vaccinations received. The expected number of children to be enrolled is ~1089 children aged 6 months–6 years and ~1055 children aged 7–14 years.

In a subset of children selected for the caregiver interview (expected number of children to be enrolled: ~914 children aged 1–6 years of age and ~787 children aged 7–14 years) we will

collect 3–4 drops of blood using a single fingerprick. The drops of blood will be applied to filter paper for determination of antibodies to select VPDs. The dried blood spots contained in paper filters will be stored in Ziploc bags and plastic containers with desiccant bags to protect against humidity. The DBS samples will be sent to CDC laboratories in the United States. Specimens will be tested using a microneutralization assay for polio and a multiplex bead assay that allows determination of antibodies levels for several VPDs (measles, rubella, tetanus, and diphtheria) and parasitic diseases (malaria, lymphatic filariasis, trachoma, yaws) for testing on dried blood spots.

All participants will be asked for consent verbally in Rohingya using a standardized script and consent document. The survey objectives, time for participation (approximately 10 minutes for completing the questionnaire and 2–3 minutes for collection of DBS samples if selected), and risks/benefits of participation will be clearly explained to all the survey participants before enrolling them in the study. Minimal risk is a result of pain or small amount of bleeding at the DBS fingerprick site in children selected for DBS sample collection. No participants will be forced to provide information or DBS samples for the study; all participation will be voluntary. Personally identifying information will not be retained in the dataset; any remaining DBS sample will be destroyed after laboratory testing is completed.

The assessment of coverage and immunity will inform about the risk of additional VPD outbreaks in the camps and the threat to spread to the nearby Bangladesh host community. Data from this serosurvey can also inform about exposures to malaria, lymphatic filariasis, and yaws in camps and settlements, indicating the need for additional control programs. The results of this assessment will benefit the FDMN population by:

- 1) Providing evidence about the remaining immunity gaps among the FDMN population in order to identify VPD risks and target future vaccination efforts, both in the FDMN population as well as the nearby host Bangladesh population;
- 2) Identifying barriers to vaccination in the FDMN population, which, in turn, will help the microplanning of future immunization activities.
- 3) Provide information useful to malaria and parasitic control programs for future activities.

## 2. Introduction

Since late August 2017, more than 650,000 Forcibly Displaced Myanmar Nationals (FDMNs) have moved into the Cox's Bazar area in Bangladesh, joining an estimated 300,000 FDMNs who had arrived during earlier waves of displacement [1]. The two pre-existing refugee camps, Kutupalong and Nayapara, and makeshift settlements have expanded with the new influx. New spontaneous settlements have also formed and are quickly growing. The dense concentration has put strain on infrastructure and services. Many partners—including the Bangladesh Ministry of Health and Family Welfare (MOH&FW), United Nations International Children's Emergency Fund (Unicef) World Health Organization (WHO), United Nations High Commissioner for Refugees (UNHCR), International Organization for Migration (IOM), Médecins Sans Frontières (MSF), and others—are working to address the health issues facing this large and vulnerable population. The February 20, 2018 Mortality and Morbidity Weekly Bulletin on the health issues facing this displaced population in Cox's Bazar in the first 7 weeks of 2018 reported large numbers of cases acute water diarrhea (36,533), acute respiratory infection (74,034), and suspected measles (713) [2].

Outbreaks of measles and diphtheria are ongoing. As of February 9, 2018, 5,560 suspected diphtheria cases and 38 deaths were reported [3]. Epidemiological data from the outbreak show that children under 15 years of age represent the highest proportion of cases at 73% [3]. Spillover of the diphtheria outbreak into the host community was reported in January 2018 [3].

In response to these events, the MOH&FW and partners managing the crisis have conducted the following activities in the camp and surrounding host communities:

- Expansion of treatment facilities to manage patients with diphtheria including administration of diphtheria antitoxin (DAT), and contact tracing for diphtheria cases;
- Implementation of Early Warning Alert and Response System (EWARS) for surveillance of diphtheria and other vaccine-preventable diseases (VPDs) at health posts within camps;
- Vaccination of new entries into Bangladesh from Myanmar with measles-rubella vaccine (MR) (6 months–14 years), and oral polio vaccine (OPV) (all ages); on Dec 23, 2017 the following antigens were added: Pentavalent vaccine (Penta) (6 weeks–6 years), pneumococcal conjugate vaccine (PCV) (6 weeks–6 years), and tetanus- diphtheria (Td) (7–14 years);
- Vaccination of close contacts of diphtheria cases at 19 fixed sites (January 2018);
- Planning for expansion of routine immunization service delivery to new health facilities in the FDMN settlement areas;
- Additionally, beginning in September, 2017, the following vaccination campaigns have taken place:

| Campaign                                                                         | Target Age         | Target Population | Coverage       | Remarks                                 |
|----------------------------------------------------------------------------------|--------------------|-------------------|----------------|-----------------------------------------|
| 1. MR, bOPV and Vitamin A campaign: 16 September-03 October 2017 (except Friday) |                    |                   |                |                                         |
| • MR                                                                             | 6 mons - <15 years | 122,580           | 135,519 (110%) | Card provided (1 st version) |
| • bOPV                                                                           | 0 - <5 years       | 47,168            | 72,334 (153%)  |                                         |
| • Vit-A                                                                          | 6 mons - <5 years  | 44,000            | 72,064 (164%)  |                                         |
| 2. OCV 1st round Campaign: 10-18 October 2017 (including Friday)                 |                    |                   |                |                                         |
| • OCV                                                                            | >1 year            | 658,371           | 700,487 (106%) | No Card, Soap provided                  |
| 3. OCV 2 nd round Campaign : 04-09 November 2017 (except Friday)      |                    |                   |                |                                         |
| • OCV                                                                            | >1 year - <5 years | 182,317           | 199,472 (109%) | No Card                                 |
| • bOPV                                                                           | 0 - <5 years       | 209,931           | 236,696 (103%) |                                         |

| Campaign                                                                                                   | Target Age         | Target Population | Coverage       | Remarks                                                   |
|------------------------------------------------------------------------------------------------------------|--------------------|-------------------|----------------|-----------------------------------------------------------|
| 4. Measles and Rubella Mop up campaign: 18 November-05 December2017 (except Friday)                        |                    |                   |                |                                                           |
| MR                                                                                                         | 6 mons - <15 years | 336,943           | 354,982 (105%) | Card provided (2 nd version)                   |
| 5. Penta, PCV, bOPV & Td campaign ( 1st round) : 12 - 31 December 2017 (except Friday)                     |                    |                   |                |                                                           |
| Penta, PCV, bOPV,                                                                                          | 6 weeks - <7years  | 185,533           | 149,962 (81%)  | Card provided (2 nd & 3 rd version) |
| Td                                                                                                         | 7 - < 15 years     | 172,007           | 165,927 (96%)  |                                                           |
| 6. Penta, PCV, bOPV & Td campaign ( 2 nd round) : 27 January – 10 February 2018 (except Friday) |                    |                   |                |                                                           |
| Penta, PCV, bOPV,                                                                                          | 6 weeks - <7years  | 185,516           |                | Card provided (2 nd & 3 rd version) |
| Td                                                                                                         | 7 - < 15 years     | 178,471           |                |                                                           |

In addition, a third round of Penta & OPV (6 weeks–7 years) and Td (7–14 years) is planned for March 2018. Upon completion of the three rounds of Pentavalent, OPV and PCV vaccination, the MOH&FW and partners plan to establish routine immunization services and conduct additional immunization campaigns as necessary in order to reach and sustain levels of

immunization coverage that protect the FDMN children from VPDs and reduce the chance of outbreaks in the settlements and surrounding host community. Although a 2015 EPI Coverage Evaluation Survey reported that 80-84% of infants in Cox's Bazar host community have received all of their scheduled vaccines, as of February 9, 2018 there have been 45 suspected diphtheria cases reported in the host community since November 2017 [3]. Bangladesh's guidelines for routine immunization do not recommend a DTP booster after three doses of DTP during infancy. Therefore, there may be a large host population living in close proximity to the FDMN settlements susceptible to VPDs as well.

In order to estimate the proportion of individuals (especially the recent arrivals) that remain un- or under-protected against the diseases targeted by the vaccination efforts, we propose to conduct an assessment of vaccination coverage and a serological assessment of immunity.

We also propose to use serological assays to measure active infection with malaria parasites and historical exposure to malaria and the neglected tropical diseases lymphatic filariasis (LF), trachoma, and yaws. The CDC multiplex assay for VPDs can include testing for these parasitic diseases without the need for additional blood collection. The Bangladesh-Myanmar border is one of the highest malaria transmission areas in South-East Asia. Estimating the burden of active infection and exposure to malaria in the FDMN population will help guide whether additional prevention and control measures, such as bednet distribution and mass screen and treat are necessary. Bangladesh and Myanmar are both endemic for LF and are implementing activities to eliminate LF as recommended by WHO. Bangladesh has met criteria to stop mass drug administration (MDA), but Myanmar still has active transmission and has not yet stopped. It is important to conduct surveillance to minimize risk of re-introduction of LF to Bangladesh. If elevated levels of antibodies to LF are found in this population, we could provide recommendations for programmatic activities in the settlements to halt ongoing transmission. Myanmar has reported reaching trachoma elimination thresholds, but limited (if any) investigation has been undertaken in Rohingya populations; living conditions following their displacement across the border are unlikely to have lessened their risk for trachoma. If elevated levels of antibodies to *Chlamydia trachomatis*, the causative agent of trachoma, are found in children in this population, we could provide recommendations for further trachoma investigations or MDA in the settlements. Although only 5,000 cases of yaws are reported each year in South-East Asia [4], the prevalence of yaws in this difficult-to-reach and underserved population may vary. Characterizing yaws transmission in the settlements is crucial for providing treatment guidelines.

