The assessment of coverage and immunity will inform about the risk of additional VPD outbreaks in the camps and the threat to spread to the nearby Bangladesh host community. Data from this serosurvey can also inform about exposures to malaria, lymphatic filariasis, and yaws in camps and settlements, indicating the need for additional control programs. The results of this assessment will benefit the FDMN population by:

- 1) Providing evidence about the remaining immunity gaps among the FDMN population in order to identify VPD risks and target future vaccination efforts, both in the FDMN population as well as the nearby host Bangladesh population;
- 2) Identifying barriers to vaccination in the FDMN population, which, in turn, will help the microplanning of future immunization activities.
- 3) Provide information useful to malaria and parasitic control programs for future activities.

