**c. Third stage sampling – Child selection**

During data collection, team members will generate a line list of children in the household aged 6m–6y and 7y–14y, ordered youngest to oldest. The team will select one child randomly (using simple random sampling) from each age group using a random number generator. Children will be assigned a unique study ID. The caregiver of the selected child(ren) will be consented, enrolled, and interviewed (if consent obtained) using the vaccination coverage assessment questionnaire. DBS samples will also be collected on selected children aged 1y–14y.

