Luminex platforms have been used for years to measure levels of multiple analytes in biological samples. Fluorescent microspheres can be readily conjugated with protein ligands, and the different spectral signatures of the labeled beads permit to include up to 100 distinct antigens in a single assay well for quantitative determinations of bound antibody. Luminex-based antibody assays are generally more sensitive than conventional ELISAs, have a wider dynamic range and are highly reproducible from assay to assay. The CDC laboratory has been developing assays for the determination of antibodies (IgG) against several vaccine preventable, parasitic, and neglected tropical diseases.

The assay in the Luminex testing includes antigens to measure protective antibody levels for tetanus, diphtheria, measles and rubella. Tetanus, diphtheria and rubella thresholds of protection are based on WHO unit value cutoffs and standards [6]. The

measles virus nucleoprotein (MV-N) is an important immune target during measles infection and has shown good potential for use in diagnostics in lieu of whole virus [7].

Antigens to be included for malaria IgG serology testing will include both short and long-term markers for exposure. For lymphatic filariasis three antigens will be used: Wb123, Bm14 and Bm33. Wb123 is specific for *Wuchereria bancrofti* the main causative agents of LF; it is highly expressed in the larval stage transmitted by mosquitos, and could be a marker of ongoing transmission. Bm14 and Bm33 are sensitive markers of any historical exposure [9].

For trachoma, two antigens derived from the causative agent *Chlamydia trachomatis* are validated for use on the MBA, pgp3 and CT694. pCT03 (pgp3) is one of the eight total ORFs on the highly-conserved cryptic plasmid which is rarely found in *Chlamydia pneumonia* isolates. CT694 is a secreted protein and has been found to be involved in pathogenesis. CT694 manipulates host proteins by acting as a T3S-dependent substrate, but its exact function is not known. At the individual level high antibody levels indicate active or previous infection. At the community level, communities with higher trachoma prevalence have higher pgp3 and CT694 antibody responses. Lack of antibody in young children in a community may be indicative of interruption of transmission by MDAs and the SAFE strategy [10].

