For yaws, two antigens will be assessed, rp17 which is a sensitive marker of historical infection and TmpA which is a marker of recent or ongoing infection. Yaws is an infectious disease caused by *Treponema pallidum* ssp. *pertenue*, which mainly affects children in rural communities in the humid tropics. WHO has targeted yaws eradication by 2020 and has developed the Morges strategy, which is comprised of mapping the disease at a community level and subsequently treating the entire population of communities where yaws is endemic. The program goals are to interrupt transmission in all countries where the disease is currently endemic and to certify that all previously endemic countries are yaws free. Detection of antibodies against rp17 and TmpA integrated into serosurveillance for other diseases can be used to provide evidence for lack of transmission of yaws following these interventions [11].

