## 10. Analysis plan

| Household vaccine coverage survey |                                                        |                                                        |                                        |
|-----------------------------------|--------------------------------------------------------|--------------------------------------------------------|----------------------------------------|
| #                                 | Result                                                 | Analysis                                               | Details                                |
| 1                                 | Denominators                                           | n/% visited, enrolled, refused, not present: flowchart | Overall, by camp, day, team, age group |
| 2                                 | Demographics                                           | n/% gender, median/range age                           | Overall, by camp & age group           |
| 3                                 | Relationship to child                                  | n/% by categories                                      | Overall, by camp & age group           |
| 4                                 | Date of arrival (if available)                         | Summarize/bar chart                                    | Compare to dates of campaigns          |
| 5                                 | Vaccine doses                                          | n/% for each antigen, divide by # of children          | Overall, by camp & age group           |
| 6                                 | Campaign participation                                 | n/% for each antigen                                   | Overall, by camp & age group           |
| 7                                 | Reasons for no vaccine, decision maker, who took child | n/% for each category, bar chart                       | Overall, by camp & age group           |
| 9                                 | Vaccines at border entry                               | n/% yes/no                                             | Overall, by camp & age group           |
| 10                                | Vaccines prior to entry                                | n/% by oral, injection, scar                           | Overall, by camp & age group           |

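### For lymphatic filariasis and yaws, the cumulative antibody markers cannot separate transmission in the settlements from exposure before arrival in children of the post-August 2017 influx

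*Protocol*

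**What the plan says.** **Population and timing.** Section 2: "Since late August 2017, more than 650,000 Forcibly Displaced Myanmar Nationals (FDMNs) have moved" into the Cox's Bazar area, "joining an estimated 300,000 FDMNs who had arrived during earlier waves of displacement". Section 8 places data and sample collection in April–May 2018. Section 5 sets the age for blood sampling: "DBS samples will also be collected on selected children aged 1y–14y", with the same rule for the registered camps.

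**Intended use.** Section 2 introduces the assays as measuring active malaria infection and historical exposure to malaria, LF, trachoma and yaws. For LF it then says that, if antibody levels are elevated, "we could provide recommendations for programmatic activities in the settlements to halt ongoing transmission". For yaws it calls it crucial to characterise transmission in the settlements. Sections 1 and 4 say that the data "can also inform about exposures to malaria, lymphatic filariasis, and yaws in camps and settlements" and so indicate a need for control programmes. The objectives in section 3 are narrower: exposure for the neglected tropical diseases (NTDs), and parasite prevalence for malaria.

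**Markers.** Section 5, on the multiplex bead assay, states for LF that "Bm14 and Bm33 are sensitive markers of any historical exposure" and for yaws describes "rp17 which is a sensitive marker of historical infection".

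**Arrival date.** The section 10 analysis plan takes arrival date only where it is available, and sets it against campaign dates. Its blood-spot rows cover denominators and vaccine immunity.

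**The concern.** Within section 2 the LF and yaws text moves from past exposure to current transmission in a particular place. A cumulative antibody marker records that exposure happened, not where. That matters little in a settled population. It matters here because much of the displaced population had arrived only months before sampling, and section 2 itself says that LF transmission is still active in Myanmar.

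If cumulative results are reported as transmission in the settlements, exposure carried in from elsewhere may be mistaken for a local signal, and a real local signal may be diluted. Arrival date is the variable that would help to separate the two. If it is not collected in the field, no later analysis can recover it.

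**Working it through.** **1. Make-up of the blood sample (the plan's own figures, section 5).** Expected number = households × share with an eligible child × (1 − household non-response) × (1 − child non-response).

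- Each registered camp: 625 × 0.60 × 0.80 × 0.90 = 270.0 (1–6 y) and 625 × 0.65 × 0.80 × 0.70 = 227.5 (7–14 y). Two camps: 2 × (270 + 228) = 996, as stated.
- Settlements: 728 × 0.60 × 0.95 × 0.90 = 373.5 and 728 × 0.60 × 0.95 × 0.80 = 332.0. Sum: 374 + 332 = 706, as stated.
- Registered-camp share: 996 / (996 + 706) = 58.5%.

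**2. Birth and residence.** Two assumptions: late August means 25–31 August 2017, and fieldwork falls between 6 April 2018 (the day after training ends) and 31 May 2018.

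- Latest birth date of a child aged 12 months on 31 May 2018: 31 May 2017. That is 86 days before 25 August 2017, so no sampled influx child was born after arrival.
- Time since arrival, m, for the earliest influx arrivals: 31 August to 6 April is 218 days, or 7.2 months; 25 August to 31 May is 279 days, or 9.2 months. Later arrivals have less.

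**3. Share of life since arrival (m / age), earliest influx arrivals.**

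| Age | m = 7.2 | m = 9.2 |
|---|---|---|
| 12 months | 60% | 76% |
| 24 months | 30% | 38% |
| 7 years | 9% | 11% |
| just under 15 years | 4% | 5% |

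For ages uniform from a to b years, the mean share is (m/12) × ln(b/a)/(b − a).

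- 1 to <7 y: ln(7)/6 = 0.324, giving 19% to 25%.
- 7 to <15 y: ln(15/7)/8 = 0.095, giving 6% to 7%.
- Weighted by 373.5 and 332.0: 13% to 17%.
- Residence exceeds half of life only below age 2m, about 14–18 months.

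**4. Share of positives acquired after arrival.** The documents do not give the forces of infection, so this share cannot be derived. As an illustration only, assume ages uniform over 1–15 years (mean 8.0), 8 months' residence (0.667 y), lasting antibody, and positives proportional to time at risk. With r the ratio of settlement to earlier force of infection, share = 0.667r / (0.667r + 7.333).

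- r = 1/3: 0.222 / 7.556 = 3%
- r = 1: 0.667 / 8.0 = 8%
- r = 3: 2.0 / 9.333 = 21%

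The spread shows that the answer follows from the assumption. The 8% is lower than the 13–17% in step 3 because it weights by person-time instead of averaging each child's share.

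**5. What the protocol says each marker shows (section 5).**

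| Marker | Protocol's description |
|---|---|
| Bm14, Bm33 (LF); rp17 (yaws) | historical |
| Wb123 (LF) | possibly ongoing transmission |
| TmpA (yaws) | recent or ongoing |
| pgp3, CT694 (trachoma) | current or past, not distinguished |
| Malaria antibodies | short- and long-term markers |
| PET-PCR | active malaria infection |

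Of the seven NTD antigens, three are called historical, two possibly ongoing or recent, and two cannot date the infection. The LF and yaws sentences in section 2 are not restricted to Wb123 and TmpA.

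**The case against.** The strongest reply is that the formal objectives claim only exposure. Transmission appears in background sentences, and the LF one is conditional. The LF rationale also includes preventing re-introduction into Bangladesh, and for that purpose infection acquired in Myanmar is part of the signal sought. The design already includes Wb123, TmpA, short-term malaria markers and PET-PCR. A breakdown by arrival date could sit in a statistical analysis plan that is not at hand.

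Much of this stands, and it rules out several stronger readings that a reader might infer:

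- **That all parasitic and NTD results are to be read as settlement transmission.** The objectives say exposure, malaria has PCR, and for trachoma section 2 proposes further investigation or mass drug administration without claiming where exposure occurred.
- **That most markers are historical.** Only three of the seven NTD antigens are so described.
- **That positives mainly reflect exposure in Myanmar.** That is an inference about cumulative markers in older influx children. It fails for the youngest, and it cannot be carried to the whole sample. Influx arrivals are 650,000 / 950,000 = 68% of the population, but about 58.5% of expected blood samples come from the two registered camps, whose mix of arrival dates is not given.

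The missing table alone would not be a finding. What the reply leaves unanswered is the wording in section 2, and the fact that an item not made mandatory before fieldwork may be lost.

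**Conclusion.** The point holds in a limited form. For LF and yaws, section 2 goes beyond what Bm14, Bm33 and rp17 can show in influx children. All of those sampled were born before arrival, and none had lived there for more than about 9 months. That conclusion rests on the protocol's dates and minimum age, with late August read as 25–31 August. The trachoma antigens share the inability to date exposure, but the protocol makes no explicit settlement-transmission claim from them.

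The 13–17% describes time, not infections, and applies to the earliest influx arrivals under uniform ages. The 3–21% illustrates assumed forces of infection and is not an estimate. The true share of positives acquired before arrival is unknown. Neither range applies to earlier arrivals, Wb123, TmpA, short-term malaria markers or PET-PCR. A secondary objective is affected; the primary coverage and immunity objectives are not.

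**What to change.** 1. In sections 1, 2 and 4, describe the cumulative antibody results as exposure wherever acquired, in line with section 3.
2. Make arrival date, or birth in Bangladesh, a required questionnaire item.
3. Add a table to section 10 giving each NTD and malaria marker by arrival before or since August 2017.
4. Base any statement on transmission in the settlements only on the markers that the protocol itself calls recent or ongoing (Wb123, TmpA, short-term malaria markers, PET-PCR), or on Bangladesh-born or long-resident children. The protocol gives no time window for these markers, so they are best read together with the table in item 3.

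The cost is a few sentences, one item already foreseen and one table, with no extra blood. The price is a narrower claim and wider intervals in the residence subgroups.
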